## Abstract

**Background:**

Measured objectively, under a quarter of adults and fewer than half of preschool children meet the criteria set in the aerobic physical activity recommendations of the Centers for Disease Control and Prevention. Moreover, adults reportedly are sedentary (seated or lying down) for most of their waking hours. Importantly, greater amounts of sedentary time on parents’ part are associated with an increased risk of more sedentary time among their children. A randomized controlled trial targeting mother-child pairs has been designed, to examine whether a movement-to-music video program may be effective in reducing sedentary time and increasing physical activity in the home environment.

**Methods:**

Mother-child pairs (child age of 4–7 years) will be recruited from among NELLI lifestyle-modification study five-year follow-up cohort participants, encompassing 14 municipalities in Pirkanmaa region, Finland.

Accelerometer and exercise diary data are to be collected for intervention and control groups at the first, second and eighth week after the baseline measurements. Background factors, physical activity, screen time, motivation to exercise, and self-reported height and weight, along with quality of life, will be assessed via questionnaires. After the baseline and first week measurements, the participants of the intervention group will receive a movement-to-music video program designed to reduce sedentary time and increase physical activity. Intervention group mother-child pairs will be instructed to exercise every other day while watching the video program over the next seven weeks. Information on experiences of the use of the movement-to-music video program will be collected 8 weeks after baseline. Effects of the intervention will be analyzed in line with the intention-to-treat principle through comparison of the changes in the main outcomes between intervention and control group participants. The study has received ethics approval from the Pirkanmaa Ethics Committee in Human Sciences.

**Discussion:**

The study will yield information on the effectiveness of movement-to-music video exercise in reducing sedentary behavior. Intervention-based methods have proven effective in increasing physical activity in home environments. Music may improve exercise adherence, which creates a possibility of achieving long-term health benefits.

**Trial registration:**

The study is registered at ClinicalTrials.gov, as NCT02270138. It was registered on October 2, 2014.

## Background

The risk of many chronic diseases, among them type 2 diabetes, obesity, breast cancer, and cardiovascular diseases, along with all causes of mortality, grows in consequence of increasing of sedentary behavior (SB) and decreasing of physical activity (PA) [1, 2]. For our research, we have slightly adapted the definitions from the Sedentary Behavior Research Network [3] and Tremblay et al. [4] thus:Sedentary behavior is any waking behavior characterized by energy expenditure ≤1.5 METs while the participant is in a sitting or reclining posture. Screen time (watching television, using a computer, and playing video games or using other screens) is included in SB.Physical activity consists of meeting the established guidelines for physical activity [5], usually reflected in achievement of at least a certain threshold (see below) number of minutes of moderate to vigorous physical activity (MVPA) per day.Physical inactivity consist of performing insufficient amounts of MVPA – i.e., not following the specified physical activity guidelines.

The Centers for Disease Control and Prevention (CDC) recommends that adults engage in at least 150 min of moderate or 75 min of vigorous intensity activity, or an equivalent combination of aerobic activities every week in bouts of 10 or more minutes. In addition, muscle-strengthening activities for all major muscle groups on two or more days per week are recommended [5]. For children, the recommendation includes at least 60 min of aerobic activity per day and muscle and bone strengthening three or more days a week [5]. In addition, there are guidelines for both adults and children to reduce SB by minimizing their sitting, screen time, and motorized transportation [6–10].

By objective measurements, under a quarter of adults [11] and fewer than half of preschool children meet the criteria set in the aerobic PA recommendations [12, 13]. Furthermore, adults seem to be sedentary (sitting or lying down) most of their waking hours [11]. In addition, larger amounts of sedentary time on the part of their parents (such as watching TV) are associated with increased risk of higher sedentary time for children [14, 15]. Lifestyle interventions (such as promoting PA) targeted at both parents and children, aimed at parents’ participation in sports, and addressing PA level, along with considering the availability of media in the home and being involved in organized activities, may generate reduction in sedentary time and a PA increase among children [16].

In the context of PA and exercise, the benefits of music have been studied mainly for therapeutic purposes and in research involving athletes and other habitual exercisers. According to these studies, listening to music can influence exercise intensity, perceived exertion, and general mood, and can help to extend workout duration [17, 18]. Only a few studies have examined the ergogenic effect of motivational music and video interventions in combination. As music does, video watching has potential to shift attention from internal stimuli to external cues [19], and motivational music with video strengthens the positive effects of audiovisual interventions [19, 20]. Increasing PA and decreasing SB represents an opportunity to prevent health problems caused by inactivity and bring long-term health benefits. Screen time is usually quite sedentary in nature, accordingly, the use of music and video together should be able to yield added benefit for increasing PA.

An experimental study entitled “Movement-to-music video program for decreasing sedentary time among mothers and children” (Moving Sound) has been prepared with the aim of reducing sedentariness by introducing motivating movement-to-music video programs for mother-child pairs. To our knowledge, changes in SB or PA have not been studied previously in relation to a movement-to-music video program in the home environment.

This article describes the rationale behind the home-based movement-to-music video program for decreasing sedentary time while increasing mother-child pairs’ PA and the methods employed.

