## Methods

### Design and ethics issues

A randomized controlled trial (RCT) is being used, with a parallel design involving one intervention and one control group of mother-child pairs. Mothers and children in the intervention group will receive a movement-to-music DVD and be instructed to exercise with it every other day. The target is to reduce SB and increase PA, in other words, sit less and be more active.

In the study, SB and PA are objectively assessed by means of an accelerometer in the first, second and eighth week of the intervention period. The accelerometers are attached to a flexible belt, which all women and children will be instructed to wear around their hips. The instructions specify using the accelerometers for 14 consecutive days (two weeks) during the participants’ waking hours at the beginning of the study and for seven days (one week) over the last week of the intervention. The accelerometers are to be removed before the participants go to bed and for showers, bathing, swimming, and other water activities. Measurements from accelerometers have been used in earlier studies for both adults and children, and they have been found to be a safe and reliable way to show changes in SB and PA [21]. There are no physical risks with the measurements in this study.

The information on the mothers’ background, motivation, and current health behavior comes from questionnaire data. The questionnaires are identical to those used in the Lifestyle, counseling, and exercise in maternity care (NELLI) five-year follow-up project.

Use of the movement-to-music video program as instructed (10–30 min every other day) will amount to less than half of adults’ and about 10–15 % of children’s PA guideline totals. The reason for this is to reduce risk of musculoskeletal injury and other complications. Moreover, when the movement-to-music video program is used in line with the instruction, there is no significant overall physical overload risk either. It is also assumed that adherence to the video protocol will be better with a short bouts of exercise compared to longer, although the evidence is contradictory [22].

Participation in the research is completely voluntary. Recruited mothers will give written informed consent for participation in the study on their and their child’s behalf. The persons recruited have the right to refuse to participate or to withdraw at any time from the study without explaining the reason.

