**Fig. 2 Fig2:**
[figure not shown]
Intervention for eight weeks

In addition, the intervention (i.e., movement-to-music) group will receive the DVD and YouTube-link to videos by e-mail or cell phone, in line with their choice between these, at the end of the first week. The DVD is the preferred option, because of the larger image and better sound when it is played through a television set. The YouTube-link is intended as an alternative to be used, for example, during trips or if the DVD breaks. Mothers in the movement-to-music group will be instructed to watch the program on the DVD or on the Internet every other day with their 4–7-year-old child. The mothers and children will be instructed to move to the video and report their exercise in the structured diaries. Mothers will also use the Brunel Music Rating Inventory-2 (BMRI-2) to assess the motivational quality of the music used in the movement-to-music video [28, 29].

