## Outcome measurements and pre-testing

### Outcomes

**The main objective** of the study is to decrease SB and increase PA among the mothers and their children by means of the movement-to-music video program.

**The primary outcomes** of the study are SB and PA, which will be assessed objectively by means of the accelerometer and further examined via the exercise diaries and questionnaires. Measurements will be performed in the first, second and eighth weeks of the intervention. For inclusion in the analysis, accelerometer data for at least four days per week and measurement time of more than 10 h per day will be needed. Participants using the accelerometer on fewer than four days per week will be excluded. Any participants whose measurement time for a given day is over 20 h will be considered to have slept with the accelerometer. To avoid possible bias in SB time, the recording time for them will be capped at 20 h, with the deduction coming from their lying-down time. The measurement discriminates among the time spent in a sitting or reclining posture, standing still, and PA. The daily amount of standing-up (breaks in sedentary time) will be calculated from the number of lying/sitting periods that end with standing. Lying, sitting, and standing time, along with light, moderate, and vigorous PA time during waking hours, will be analyzed both in minutes and as a proportion of the measurement time (at least 10 h per day). In the analysis, moderate and vigorous activity might be combined as MVPA if vigorous PA covers a very small proportion of the total measurement time.

**Secondary outcomes** of the study include the quantity of self-reported sitting and screen time among mothers and children, motivation to exercise, and the motivational quality of the music and movement-to-music video. Additional secondary outcomes are mother’s weight and quality of life, depression, anxiety, perceived health, and work ability assessed by a questionnaire.

**The specific aim** is to study the effectiveness of the intervention by comparing accelerometer use alone with a combination of accelerometer and movement-to-music video program for mother-child pairs.

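### Sedentary behaviour is defined to include all screen time, but the intervention is exercise to a screen, so the self-reported screen-time outcome can absorb study-video minutes in one arm only

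*Protocol article*

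**What the plan says.** All references are to the protocol article.

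- **Definition (Background).** The first sentence sets two conditions: "Sedentary behavior is any waking behavior characterized by energy expenditure ≤1.5 METs while the participant is in a sitting or reclining posture". The next carries neither of them: "Screen time (watching television, using a computer, and playing video games or using other screens) is included in SB". Later in the same section the authors are more guarded: "Screen time is usually quite sedentary in nature, accordingly, the use of music and video together should be able to yield added benefit for increasing" physical activity.
- **Intervention (The interventions; Design and ethics issues).** Intervention mothers are "instructed to watch the program on the DVD or on the Internet every other day with their 4–7-year-old child". The DVD, played through a television set, is preferred to the YouTube link. Use is active: "The mothers and children will be instructed to move to the video and report their exercise in the structured diaries". The instructed amount is "10–30 min every other day". Controls receive no video.
- **Outcome (Outcomes; Questionnaires).** The secondary outcomes include "the quantity of self-reported sitting and screen time among mothers and children". These items are collected at baseline and week 8 in both arms.
- **Instruments (Design and ethics issues; Questionnaires).** The mothers' questionnaires are described as identical to those of the parent cohort's five-year follow-up. The child's items are based on a national health-monitoring questionnaire. No adaptation of the screen-time items is described, whereas the adaptation of the exercise-enjoyment items is.

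**The concern.** Taken literally, the two definition sentences classify the same minutes in opposite ways. A mother and child jumping and squatting in front of the television are not sedentary under the posture and energy condition. They are sedentary under the screen-time sentence. For most screen use the gap would be harmless, but here the treatment is itself screen use and only one arm is told to do it.

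The place where this can do damage is the self-reported screen-time outcome. If general screen-time items are answered with the study video included, the intervention arm's week-8 figure contains treatment minutes and the control arm's does not. A null or adverse result could then be produced by the treatment being counted as the behaviour it is meant to replace. It could also disagree with the accelerometer result for a purely definitional reason.

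**Working it through.** **1. Is the primary outcome touched?**

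Outcomes and Accelerometer measures describe a posture-based measurement that separates sitting or reclining, standing still and physical activity. Power calculations defines sedentary time as sitting or lying down, with a mean of 460 min/day. Table 1 can be reproduced on that basis, with n per group = 2(z₀.₉₇₅ + z₀.₈₀)² / (difference/SD)²:

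- 25 min, SD 70: 2(1.960 + 0.842)² / 0.357² ≈ 123.1, rounded up to 124.
- 30 min, SD 60: 2(1.960 + 0.842)² / 0.500² ≈ 62.8, rounded up to 63.
- The other four rows give 107, 91, 86 and 74, as printed.

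No screen-time quantity enters. Upright movement to the video is not sedentary in this measure, so Table 1 stands at 63–124 pairs per group.

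**2. How many minutes can enter the screen-time outcome?**

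Every other day is 3.5 sessions a week.

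| Session length | Source | Per week | Per day |
|---|---|---|---|
| 10 min | Design and ethics issues (lower); also one of the two shorter videos | 3.5 × 10 = 35 min | 35/7 = 5 min |
| 12 min | the third video (DVD production section) | 3.5 × 12 = 42 min | 42/7 = 6 min |
| 30 min | Design and ethics issues (upper) | 3.5 × 30 = 105 min | 105/7 = 15 min |

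In the control arm the figure is 0.

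**3. What does that do to the comparison?**

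Let V be the prescribed video minutes per day, a the share of prescribed use carried out, p the share of those minutes that the mother includes in the answer, and ΔS the true change in seated screen time. In the intervention arm:

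recorded change = ΔS + a·p·V

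The error as a measure of seated screen time is a·p·V. It runs from 0 (p = 0) to V (a = p = 1), so from 0 up to 5–15 min/day depending on session length. The document gives neither a nor p.

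Whether the video replaces other viewing changes ΔS but not the error. With a = p = 1:

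- Video replaces seated viewing minute for minute: ΔS = −V, so the recorded change is 0. A true fall of 5–15 min/day disappears.
- Video is additional: ΔS = 0, so the recorded change is +V. Screen time appears to rise by 5–15 min/day.
- Any true fall smaller than V is recorded as a rise.

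**4. Scale.**

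The document gives no target difference or SD for screen time, so the error cannot be expressed as an effect size for that outcome. For orientation only, 5–15 min/day is 5/30 = 17 % to 15/25 = 60 % of the 25–30 min/day difference assumed for total accelerometer sedentary time, which is a different outcome.

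**The case against.** A reader might infer that following the plan scores the treatment as sedentary time, so that the primary result is biased and underpowered. If 5 or 15 min/day really were added to sedentary time in one arm, power at the Table 1 sample sizes would fall from 80 % to about 61–65 % or 20–29 %. The documents do not support that reading. The primary measure scores posture, the sample size rests on sitting or lying, and nowhere are self-reported screen minutes converted into sedentary minutes. Outcomes does say that the primary outcomes are further examined through diaries and questionnaires, but it gives no scoring rule for doing so.

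A second over-reading is that the screen-time result is certain to be biased. The strongest case against that has four parts:

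- The item wording is not reproduced, and an article commonly leaves it to fuller documents. Mothers may not think of exercising to a video as screen time. This stands, and it is why the range starts at 0.
- The mothers' instrument is chiefly about sitting in various contexts, where upright exercise has no place, and the child's has separate questions for exercise and for screen time. This stands in part. It makes the problem less likely for mothers, but Questionnaires also lists screen time among the items collected, and a separate exercise question does not stop the same minutes being entered under both.
- The video may replace ordinary viewing, so recorded screen time need not rise. True, but the error as a measure of seated screen time is unchanged, and a real fall is then hidden.
- Fifteen minutes a day needs 30 min sessions, full adherence and full reporting. True. One video per session gives 5–6 min/day at most.

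Statistical methods does not list screen time among the outcomes compared between arms. The comparison is inferred from its status as a secondary outcome collected in both arms.

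**Conclusion.** The point holds for the definition and for one named secondary outcome. The screen-time sentence in the Background lacks the posture condition of the sentence before it, and the described instruments give no sign of separating study-video minutes from other screen use. In the intervention arm only, seated screen time can therefore be overstated by between 0 and 5–15 min/day, and by at most about 5–6 min/day if one 10–12 min video is used per session. Where the error is not zero, it works against the intervention. The range assumes use as instructed. The true figure depends on adherence and on how mothers answer, neither of which the document gives.

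The primary accelerometer outcome, the power calculation and the main conclusion are not affected. What is at risk is the interpretation of a null or adverse screen-time result, most of all the child's.

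**What to change.** 1. **Definition.** State that sedentary behaviour includes only screen time spent sitting or reclining. This is one clause, and it brings the sentence into line with the accelerometer measure.
2. **Follow-up forms.** Leave the existing screen-time items unchanged, so that week 8 stays comparable with baseline and with the parent cohort. Add one item for the intervention group, for the mother's and the child's answers separately, asking how much study-video time was included. Table 3 already has intervention-only items at weeks 2 and 8, so it can sit there. The included minutes can then be excluded from the outcome.
3. **Forms already completed.** Recruitment began in November 2014, so some will lack the item. For these, report a sensitivity analysis that subtracts the diary-recorded video minutes of weeks 2 and 8. Present it as a bound beside the unadjusted result and not as the main analysis, because subtracting from mothers who never counted the video creates the opposite error.

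The cost is one clause, one short item and one derived variable from diaries already collected. The downside is that it relies on respondents or diary entries identifying the video sessions. The mothers' diary asks for start and end times of exercise. The child's is described only as exercise time at daycare or school and at home and time spent in physical activity, so video sessions may be harder to pick out there.

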## Methods

### Design and ethics issues

A randomized controlled trial (RCT) is being used, with a parallel design involving one intervention and one control group of mother-child pairs. Mothers and children in the intervention group will receive a movement-to-music DVD and be instructed to exercise with it every other day. The target is to reduce SB and increase PA, in other words, sit less and be more active.

In the study, SB and PA are objectively assessed by means of an accelerometer in the first, second and eighth week of the intervention period. The accelerometers are attached to a flexible belt, which all women and children will be instructed to wear around their hips. The instructions specify using the accelerometers for 14 consecutive days (two weeks) during the participants’ waking hours at the beginning of the study and for seven days (one week) over the last week of the intervention. The accelerometers are to be removed before the participants go to bed and for showers, bathing, swimming, and other water activities. Measurements from accelerometers have been used in earlier studies for both adults and children, and they have been found to be a safe and reliable way to show changes in SB and PA [21]. There are no physical risks with the measurements in this study.

The information on the mothers’ background, motivation, and current health behavior comes from questionnaire data. The questionnaires are identical to those used in the Lifestyle, counseling, and exercise in maternity care (NELLI) five-year follow-up project.

Use of the movement-to-music video program as instructed (10–30 min every other day) will amount to less than half of adults’ and about 10–15 % of children’s PA guideline totals. The reason for this is to reduce risk of musculoskeletal injury and other complications. Moreover, when the movement-to-music video program is used in line with the instruction, there is no significant overall physical overload risk either. It is also assumed that adherence to the video protocol will be better with a short bouts of exercise compared to longer, although the evidence is contradictory [22].

Participation in the research is completely voluntary. Recruited mothers will give written informed consent for participation in the study on their and their child’s behalf. The persons recruited have the right to refuse to participate or to withdraw at any time from the study without explaining the reason.

This research project will be carried out in accordance with good scientific practice, with respect to ethics issues also. The UKK Institute for Health Promotion Research, based in Tampere, Finland, owns the data and is responsible for its storage and use.

The Pirkanmaa Ethics Committee in Human Sciences has issued a favorable statement on the Moving Sound study (statement 23/2014).

